The generalisability of the intervention will be based on collaboration with the Délégués de l'Assurance Maladie (DAM), who are already working on this issue on an operational and regular basis throughout France [42]. The DAMs, who are based throughout the country, make regular visits to GPs and promote good practice [43]. As this method of visiting GPs is original on an international scale, it is vital to demonstrate its impact on practices.

**The aim of the research** is to evaluate the effect of multifaceted interventions on GP prescribing by comparing the volumes of antibiotics dispensed at the end of 12 months of follow-up in a study comparing :

i) an intervention carried out by the Délégués d'Assurance Maladie (health insurance representatives) in general practices, combining a usual visit (with awareness-raising on antibiotic resistance, work on preconceived ideas, feedback on practices) and a demonstration of the use of Antibioclic (arm 1),

ii) an intervention carried out in the same way by Health Insurance delegates but without demonstration of Antibioclic (arm 2),

iii) compared with usual practice (arm 3).

1. **ORIGINALITY AND INNOVATION**

The project proposes an original study based on collaboration between various primary care players: a university team of general practitioners, regional health insurance teams in Pays de la Loire, a university hospital infectiology team, the MedQual centre (Antibiotic Resource Centre for the Pays de la Loire region) and the Antibioclic Clinical Decision Support System team.

The project was co-constructed with the Pays de la Loire health insurance scheme.

The originality of the intervention lies in the approach combining the strengths of tools that already exist and are established, but which act without synergy, despite their strong potential added value: face-to-face interventions by Assurance Maladie delegates in doctors' surgeries, support materials (enabling feedback on practices) built from prescription data collected by Assurance Maladie, and the Antibioclic internet tool to help with prescribing.

The robust design of a randomised study in 3 parallel arms covering the entire population of GPs in an administrative region will enable us to conclude both on the effect of a specific intervention by health insurance delegates in the form of the usual visits implemented by the social security system, and on the specific added value of demonstrating the use of Antibioclic.

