***4.1.1. Main objective***

The main objective is to compare the effect on antibiotic dispensing after 12 months of follow-up,

i) an intervention carried out by the Délégués d'Assurance Maladie in general practices, combining a routine visit (raising awareness of antimicrobial resistance, work on preconceived ideas, feedback on practices) and a demonstration of the use of Antibioclic (arm 1),

ii) an intervention carried out in the same way by the Health Insurance delegates, but without Antibioclic being demonstrated (arm 2),

iii) compared to usual practice (arm 3). In the latter arm, the Health Insurance delegates carry out a visit that does NOT involve prescribing antibiotics.

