
- 1. ***Inclusion criteria***

GPs practising in one of the 5 study departments who had seen at least 100 different patients (of any age) in the year preceding the evaluation.

- 1. ***Non-inclusion criteria***

Not included:

. doctors with special practices (acupuncture, allergology, angiology). These doctors will be identified on the basis of health insurance data.

. doctors included in another programme to improve antibiotic prescribing practices run by the Assurance Maladie in the form of a "Plan Personnalisé d'Accompagnement" (CPAM initiative).

. doctors who participated in the design of the study: doctors who took part in the steering groups and working groups, doctors who tested the content of the DAM visit.

1. **DESIGN AND CONDUCT OF THE STUDY**
   1. ***General research methodology***

. This will be a prospective, randomised, controlled, open-label study with 3 parallel arms.

. The study will involve all GPs in the 5 departments of the Pays de la Loire region who meet the inclusion and non-inclusion criteria.

. The statistical unit will be the doctor.

. The source of the data will be the Health Insurance SNDS database for the Pays de la Loire region.

. Randomisation will be based on doctors' surgeries (and not doctors) to limit confounding bias between arms.

. The analysis will be carried out on an intention-to-treat basis.

This is a 'real-life' study.

In particular, it will not be a question of evaluating the effectiveness of the Antibioclic site "*per* protocol".

The challenge will be to assess the effect of the 2 interventions, compared with usual practice, bearing in mind that the Health Insurance Representatives' visit and its potential impact will vary greatly from one doctor to another.

- 1. ***RANDOMISATION; INTERVENTION ARMS and CONTROL ARMS***

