**Initial collection**

The Assurance Maladie will be responsible for extracting the data specific to the research and for building up the database.

The data collected will be data characterising GPs: age group (in 5-year increments from the age of 25), sex, classification of the commune of practice (according to INSEE urban area zoning, "major centres" (codes 111, 112, 120), "small centres" (codes 211, 212, 221, 222), "isolated towns" (code 400), and "other communes" (code 300) [46]), activity in terms of number of annual consultations, number of patients in the GP patient base, mode of practice (alone, in a group).

The Assurance Maladie randomises the GPs' places of practice and adds the allocated randomisation arm to the list of participating GPs, according to their place of practice.

The Assurance Maladie extracts data on antibiotic therapy prescriptions from all GPs included in the study (data for the 12 months preceding the visit) for descriptive purposes (T0).

**A 2nd round of** data **collection** will take place at the end of 12 months' follow-up: the French National Health Insurance will extract data on the dispensing of antibiotics prescribed by all GPs included in the study.

The data collection period will begin on the day of the DAM's visit.

- - 1. ***PARTICIPANT IDENTIFICATION***

The data will be centralised by the Assurance Maladie. No nominative data will be exported outside the databases of the Sickness Insurance departments.

The variables were selected after a pilot study, and the health insurance authorities paid close attention to CNIL regulations, to ensure that no data was directly identifiable (which is why the ages of practitioners are grouped into 5-year classes, and the communes classified by type).

- 1. ***Statistics***
     1. ***DESCRIPTION OF PLANNED STATISTICAL METHODS, INCLUDING TIMETABLE FOR INTERIM ANALYSES***

The analyses will be carried out using R 3.6.0 software.

The data will be described by the numbers and percentages of each modality for the qualitative variables and by the minimum, maximum, quartile, mean and standard deviation for the quantitative variables, overall and according to the 3 randomisation arms.

A hierarchical procedure will be used to successively test the comparison between the 3 arms, while maintaining a 5% alpha risk. The first hypothesis tested will be the difference between arm 1 and arm 3. If the test is significant, a second test will be performed comparing arm 1 to arm 2.

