Given that two strategies will be compared with current practice, it may be necessary to estimate several incremental cost-effectiveness ratios (ICERs). A dominance analysis will be carried out to check whether certain interventions are dominated, i.e. more costly and less effective than another intervention. The average incremental cost-effectiveness ratio will be presented, together with its 95% confidence interval.

Univariate and multivariate sensitivity analyses will be carried out to check the robustness of the results to changes in assumptions about certain study parameters.

- 1. ***HEALTHCARE CONSUMPTION AND VALUATION***

The costs of the three strategies compared will be estimated in three stages [48]:

. collection of resources consumed,

. the unit monetary value of resources,

. estimated total costs.

Deliveries and costs of systemic antibiotics will be estimated using information retrieved from SNDS databases extracted by the Assurance Maladie in Pays de la Loire. The resources consumed will be valued at Assurance Maladie prices for drugs.

The resources used as part of the study will include :

. the costs associated with preparing and holding the training course,

. training time for DAMs,

. the development of communication material,

- the time it takes to create a digital visual aid,

- time for role-playing,

- the time it takes to write a sales pitch,

- time to rewrite the memo cards.

. time doctors

. the average duration of use of Antibioclic by doctors

We will take into account antibiotic dispensing based on the doctor's prescription and the monitoring of activity over a 12-month period. The costs will be calculated using Assurance Maladie tariffs.

This will be done by combining the results of the two previous stages. Given the 12-month time horizon, the costs will not be discounted. We will present the average costs per patient in each arm.

- 1. ***Efficiency data***

Effectiveness will be measured by the ratio between deliveries of defined daily doses (DDD) observed in the Assurance Maladie databases and the WHO defined daily doses between the different scenarios in the analysis [46-47].

We will look at defined daily doses (DDD) of all types of systemic antibiotics for all patients per 100 consultations [51]. To do this, we will stratify by specific antibiotic types (ie, tetracyclines, quinolones, β. lactamine/penicillin, other β. lactamine, other antibacterials, unspecified, etc.).

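### The confirmatory hierarchy gives arm 2 v arm 3 no error-controlled test, although the protocol says it will conclude on the delegate visit itself

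*Protocol*

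**What the plan says.** Under the description of planned statistical methods, the protocol states: "A hierarchical procedure will be used to successively test the comparison between the 3 arms, while maintaining a 5% alpha risk". It then names the steps. The opening one sets arm 1 against arm 3. The other depends on its result: "If the test is significant, a second test will be performed comparing arm 1 to arm 2". No third step follows.

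The aims are set out in several places:

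- **Originality and innovation:** the design "will enable us to conclude both on the effect of a specific intervention by health insurance delegates in the form of the usual visits", and also on the specific added value of demonstrating Antibioclic.
- **Description of expected benefits:** results are promised on the specific impact of two types of intervention, with delegate visits listed first.
- **4.1.1 Main objective:** arm 1 and arm 2 are listed, followed by usual practice (arm 3) as comparator. Pairs are not named.
- **General research methodology:** "The challenge will be to assess the effect of the 2 interventions, compared with usual practice".
- **Medico-economic study:** "Given that two strategies will be compared with current practice", several incremental ratios may be needed. The secondary evaluation criteria define the ratio as a comparison of all three alternatives.

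The paragraph on the primary endpoint in the statistics section says that volumes are compared between arms by Student's t test, without naming pairs.

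**The concern.** The three arms allow three pairwise contrasts, and each answers a different question. Arm 1 v arm 3 estimates the visit plus the Antibioclic demonstration. Arm 1 v arm 2 estimates the demonstration against paper memos, with the visit common to both. Arm 2 v arm 3 estimates the visit without Antibioclic. The hierarchy contains the first two only.

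The two planned tests cannot stand in for the third. A significant arm 1 v arm 3 followed by a non-significant arm 1 v arm 2 does not show that arm 2 is better than usual practice, because failing to find a difference between arms 1 and 2 does not make them equivalent.

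At stake is the case where the visit works and the demonstration adds little. A payer would then most want a firm answer on the simpler arm, and the plan provides no formal test of it.

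**Working it through.** **Inputs.** From the justification of the number of inclusions: SD 5,360 DDD, ICC 0.05, 1.9 GPs per practice, 2,400 doctors, power 80%, alpha 5%, detectable difference 450 DDD. Allocation is 1:1:1, so about 800 doctors per arm. Sidedness is not stated; two-sided is assumed.

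**Step 1. Standard error and the plan's own figure.**
Design effect = 1 + (1.9 − 1) × 0.05 = 1.045.
SE of a difference between two arms = 5,360 × √(2 × 1.045 / 800) ≈ 274 DDD.
Detectable difference at 80% power = (1.960 + 0.842) × 274 ≈ 767 DDD.
The stated 450 DDD is therefore not reproduced; power at 450 is about 37.5%. That is a separate matter and the present point does not depend on it, but it is why results are shown at both 450 and 767 DDD.

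**Step 2. What the planned hierarchy delivers.** Three pairwise z tests sharing arm means were simulated (1,000,000 runs, inputs as above), with both interventions equally effective:

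| Common reduction | Stops at arm 1 v 3 | Passes, then arm 1 v 2 not significant | Passes, then arm 1 v 2 significant |
|---|---|---|---|
| 450 DDD | 62.5% | 37.5% − 2.2% = 35.3% | 2.2% |
| 767 DDD | 20.0% | 80.0% − 3.4% = 76.7% (unrounded inputs) | 3.4% |

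Among trials that pass the first test, the share ending at a non-significant arm 1 v arm 2 is 1 − 0.0219/0.3751 = 94.2% at 450 DDD and 1 − 0.0335/0.8004 = 95.8% at 767 DDD. The share of trials with a formal test of arm 2 v arm 3 is zero in every column, by design.

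**Step 3. Can the missing test be added without splitting alpha?** Keep arm 1 v arm 3 as the gate at 5%. Once it is passed, test arm 1 v arm 2 and arm 2 v arm 3, each at 5%.

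- If arm 1 truly equals arm 3, any rejection requires a false rejection at the gate, which has probability at most 5%.
- If arm 1 truly differs from arm 3, then arm 1 = arm 2 and arm 2 = arm 3 cannot both be true. At most one true null remains, and it is tested at 5%.

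Familywise error is therefore at most 5%, provided each single test holds its own level. The simulation gave 5.0% under the global null. With one true later null it gave 3.4% when arm 2 equals arm 3 and arm 1 is 767 DDD lower, and likewise 3.4% when arms 1 and 2 are both 767 DDD below arm 3. By contrast, an unadjusted arm 2 v arm 3 test run beside the gate gives 9.0% under the global null for those two tests.

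**Step 4. Where the test is placed matters.** Power for arm 2 v arm 3:

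| True reductions (arm 1, arm 2) | Directly behind the gate | Third, behind arm 1 v arm 2 |
|---|---|---|
| 450, 450 | 22% | 0.2% |
| 767, 767 | 69% | 1.8% |
| 900, 450 | 37% | 6.8% |
| 1,535, 767 | 80% | 61% |

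A third step behind arm 1 v arm 2 fails in exactly the case where the answer is most wanted.

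**The case against.** The strongest reply is that the choice of confirmatory contrasts belongs to the sponsor. The rationale describes one multifaceted intervention, visit and Antibioclic together. On that view, testing the package first and the added value second is coherent. Both planned tests are legitimate and the 5% risk is held. This stands: the hierarchy is not invalid. What remains is that it does not match the aims stated elsewhere, and rewording those aims would also resolve the mismatch.

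A second reply is that arm 2 v arm 3 is not shut out. The statistics section compares volumes between arms without excluding a pair, and the economic section foresees differences in efficacy with 95% confidence intervals. This also stands in part. A reader might infer that the trial can say nothing about the visit alone, or could neither recommend nor reject arm 2. The documents do not support that: an estimate with an interval remains possible. But reading a test of this pair into the phrase about comparing arms puts it outside the procedure meant to hold the 5% risk, at the 9.0% cost shown above.

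A third reply is that such detail belongs in the statistical analysis plan. It does not hold here, because the protocol itself fixes the two steps.

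Finally, the added test would often be inconclusive: 22% power at the protocol's own 450 DDD. This is correct, and it is a reason to report the interval whatever the result.

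**Conclusion.** The point holds as a mismatch between the stated aims and the confirmatory hierarchy, and it should be fixed. Arm 2 v arm 3, the only contrast that isolates the visit without Antibioclic, has no pre-specified, alpha-controlled test on the primary endpoint under any outcome.

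Three stronger readings are not supported. A reader might take the 94-96% as a share of all trials. It applies only to those that pass the first test; of all trials, 35% stop at arm 1 v arm 2 at 450 DDD and 77% at 767 DDD. A reader might also say that the main objective itself promises this contrast. That section lists the arms and the comparator without naming pairs; the explicit promise to conclude on the visit stands under originality and innovation, supported by the general methodology and expected-benefits sections. Lastly, the economic section does not commit firmly to a ratio for arm 2 v arm 3, although the secondary criteria do set all three alternatives against each other.

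The text comparison needs no assumption. The percentages rest on the protocol's SD, ICC and practice size, 800 doctors per arm, normal test statistics, two-sided 5%, and each test holding its nominal level.

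**What to change.** In the statistics section, keep arm 1 v arm 3 as the first test at 5%. State that, if it is significant, arm 1 v arm 2 and arm 2 v arm 3 are each tested at two-sided 5% without further adjustment, and that both are confirmatory for the primary endpoint. Do not place arm 2 v arm 3 behind arm 1 v arm 2. State also that the arm 2 v arm 3 difference and its 95% confidence interval are reported whatever the tests show.

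This takes a sentence or two. It needs no further data, costs no alpha and takes no power from the two planned tests. It leaves one limit: if the gate fails, arm 2 v arm 3 again has no formal test.

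If the sponsor does not want this contrast to be confirmatory, reword the sections on originality and innovation, expected benefits, main objective and general research methodology so that the effect of the visit alone is described as descriptive. Either change should be made before the outcome data are analysed.

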- - - 1. *Primary endpoint*

The overall volume of systemic antibiotics dispensed in DDD at the end of 12 months of follow-up, per participating doctor, will be calculated and compared between arms using a Student's t test.

- - - 1. *Secondary endpoints*

In addition to the primary endpoint (assessing the overall volume of systemic antibiotics dispensed at 12 months follow-up), other endpoints will be studied.

1/ The overall volume of systemic antibiotics dispensed in DDD at the end of 3 months of follow-up, per participating physician, will be calculated and compared between arms using a Student's t test. The monthly change in the overall volume of systemic antibiotics dispensed will also be described between arms.

2/ The volume of broad-spectrum systemic antibiotics most frequently responsible for antibiotic resistance in primary care (3^ème^ generation cephalosporins, fluoroquinolones, amoxicillin/clavulanic acid) dispensed in DDD per participating doctor will be calculated and described monthly and over 12 months of follow-up, and for the latter, compared between arms using a Student's t test.

3/ Sub-group analyses :

. Subgroup 1: The volume of systemic antibiotics dispensed to patients aged over 65 in DDD at the end of 12 months of follow-up, per participating doctor, will be calculated and compared between arms using a Student's t test.

. Subgroup 2: the same analysis will be carried out for patients under 6 years of age, and for these same patients on the broad-spectrum systemic antibiotics most frequently responsible for antibiotic resistance in primary care.

The monthly trends for these two sub-groups will also be described according to the randomisation arms.

The overall monthly volume of systemic antibiotics dispensed in DDDs, and by subgroup, will be described for each of the three groups, and represented graphically.

4/ The characteristics of the physicians (age, sex, type of practice, etc.), which may be associated with the overall prescription of systemic antibiotics, will also be investigated using ANCOVA models, adjusted for the randomisation arm.

5/ The secondary endpoints used for the medico-economic analysis are described in section 9. Medico-economic analysis, and in particular chapters 9.2, 9.3 and 9.4.

. The cost-effectiveness analysis will be conducted on the intention-to-treat (ITT) population, i.e. on all randomised healthcare professionals.

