. Details of the resources consumed in each arm (averages and dispersion) and the average costs and efficiency per doctor will be calculated for each arm.

. A table will show the difference between the two groups in terms of costs and effectiveness, and the cost-effectiveness ratio will be calculated.

. As costs are not generally distributed according to a normal distribution, the incremental cost-effectiveness ratio and its confidence interval will be estimated using the non-parametric bootstrap method [49].

Finally, the probability that the use of antibioclic associated with a specific DAM visit is cost-effective compared with *a standard DAM visit* will be calculated for different values of willingness to pay for a reduction in antibiotics.

- - 1. ***STATISTICAL JUSTIFICATION FOR THE NUMBER OF INCLUSIONS***

After preliminary work to explore feasibility with the Assurance Maladie teams, the number of eligible doctors was estimated at 2,400 GPs who saw more than 100 different patients in 2018. The average number of DDDs dispensed per doctor in 2018 was 7,671, with a standard deviation of 5,360. In 2018, the average number of DDDs dispensed per doctor was 7671, with a standard deviation of 5360. Due to cluster randomisation, an inflation factor must be applied to calculate the number of subjects. In a previous study in the Loire Atlantique and Vendée regions [47], the average number of GPs per practice was 1.9. We set an intra-class correlation coefficient of 0.05 [50].

With an alpha risk of 5% and power of 80%, we can then demonstrate a significant difference if we have at least an average difference of 450 DDD per doctor (over the 12 months following the DAM visit) between the arms being compared.

- 1. ***Expected degree of statistical significance***

The alpha risk is set at 5%.

- 1. ***Method for taking into account missing, unused or invalid data***

All analyses will be performed on an intention-to-treat (ITT) basis.

The volumes of systemic antibiotics dispensed attributed to doctors who ceased their activity (end of career, moving outside the region, death, etc.) during the study follow-up period will be replaced by multiple imputation. A sensitivity analysis of the per-protocol population will also be carried out, excluding these doctors, as well as those who did not receive a visit from the DAM, and those who were not computerised.

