For doctors who have not been visited by the DAMs, the start date of the data collection period will be allocated by drawing lots, and staggered over the 3 months (start date based on the visit dates available for the 3 randomisation arms).

- 1. ***Randomisation***

The Assurance Maladie will generate a list of GP practices that meet the inclusion criteria. It will then randomise the GP practices on a 1:1:1 basis. Doctors will be assigned to the randomisation arm to which their practice has been allocated.

1. **SAFETY / UNDESIRABLE EFFECT**

In the regulatory sense and within the meaning of the Jardé Law, this study does not constitute research involving human subjects. In the regulatory sense and within the meaning of the Jardé Law, this protocol does not involve any change in the usual management of patients, so any adverse events or effects observed will be unrelated to the study.

1. **MEDICO-ECONOMIC STUDY**

This section presents the objectives and methodology of the efficiency analysis, based on a cost-effectiveness analysis. The economic evaluation methodology follows the 2011 recommendations of the French National Authority for Health [49].

- 1. ***Objective, perspective and time horizon of the cost-effectiveness analysis***

The study involves a cost-effectiveness analysis comparing the delivery of antibiotics over a 12-month period in current practice, compared with two alternative strategies

i) an intervention carried out by the Délégués d'Assurance Maladie (Health Insurance Representatives) in general practices, combining a regular visit (with awareness-raising on antibiotic resistance, work on preconceived ideas, feedback on practices) and a demonstration of the use of Antibioclic,

1. an intervention carried out in the same way by the Délégués d'Assurance Maladie, but without Antibioclic being demonstrated.

This analysis will be carried out from the point of view of the Assurance Maladie Obligatoire over a 12-month period.

Costs will be estimated on the basis of information retrieved from the SNDS databases extracted by the Assurance Maladie in Pays de la Loire. The resources consumed will be valued at Assurance Maladie prices for drugs.

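### Practices are randomised, but the primary and main secondary volumes are compared by an ordinary doctor-level t test, so the claimed 5% alpha is slightly exceeded (about 5.5% at the protocol's own inputs)

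*Protocol*

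**What the plan says.** **Unit of randomisation.** Under General research methodology the protocol states: "Randomisation will be based on doctors' surgeries (and not doctors) to limit confounding bias between arms". The Randomisation section of the data management and statistics chapter adds, of the health insurer: "It will then randomise the GP practices on a 1:1:1 basis", and then: "Doctors will be assigned to the randomisation arm to which their practice has been allocated". All doctors of one practice are therefore in one arm.

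**Unit of analysis.** General research methodology also states: "The statistical unit will be the doctor".

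**Test.** In the Statistics section, under Primary endpoint, the 12-month volume in DDD "per participating doctor, will be calculated and compared between arms using a Student's t test". Under Secondary endpoints the same test is named for the 3-month volume, the 12-month broad-spectrum volume, the volume in patients over 65, and the volume in children under 6 (for these children also the broad-spectrum volume). No adjustment for practice is mentioned.

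**Alpha.** The opening of the Statistics section sets a hierarchical procedure (arm 1 against arm 3, then arm 1 against arm 2) that is said to hold alpha at 5%.

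**Sample size.** The statistical justification for the number of inclusions recognises the clustering: "Due to cluster randomisation, an inflation factor must be applied to calculate the number of subjects". It takes 1.9 GPs per practice and an intra-class correlation of 0.05.

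**The concern.** The protocol assumes that doctors in the same practice are correlated when it sizes the trial, and that they are independent when it tests the result. Both cannot be right. With a positive correlation, the variance of an arm mean is larger than the t test supposes. The standard error is then too small, the interval too narrow and the p-value too small.

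At stake is the confirmatory claim. Both steps of the hierarchy use the same unadjusted test, so ordering them cannot restore the stated 5%. A result near the threshold could be declared significant when an analysis that respects the design would not support it. Cluster randomisation analysed as if individual is also an easy target for any reader of the eventual report.

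**Working it through.** **Inputs from the protocol (sample-size section unless noted).** Mean practice size m = 1.9; intra-class correlation ICC = 0.05; SD 5,360 DDD per doctor; 2,400 doctors, which at 1:1:1 by practice is about 800 per arm; alpha 5%, power 80%. Sidedness is not stated; two-sided is assumed here.

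**Step 1: the plan's own figures.**
- *The 5% alpha.* A simulation with 421 practices per arm (800 / 1.9) and 20,000 runs gave a rejection rate of 5.0% (near-equal sizes) and 5.2% (geometric sizes, mean 1.9) at ICC = 0. The claim is right if doctors are independent.
- *The 450 DDD detectable difference.* Difference = (1.960 + 0.842) × 5,360 × √(DE × 2/800). This gives 750.8 with DE = 1 and 767.5 with DE = 1.045. Neither reproduces 450. That is a separate matter and carries no weight here, but it means the stated difference does not show how the inflation factor was applied.

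**Step 2: design effect at the protocol's inputs, equal practice sizes.**

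DE = 1 + (m − 1) × ICC = 1 + 0.9 × 0.05 = 1.045.

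True SE / t-test SE = √1.045 = 1.022, so the t-test interval is 1 − 1/1.022 ≈ 2.2% too narrow.

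True alpha = 2 × [1 − Φ(1.96 / 1.022)] = 2 × [1 − Φ(1.917)] = 0.055.

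**Step 3: unequal practice sizes, same ICC.** The protocol records both solo and group practice (Secondary evaluation criteria, item 4; Initial collection), so sizes differ, but it gives no distribution. The coefficient of variation (CV) below is an assumption.

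DE = 1 + [(1 + CV²) × m − 1] × ICC

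| CV (assumed) | DE at ICC 0.05 | Interval too narrow by | True alpha |
| --- | --- | --- | --- |
| 0 | 1.045 | 2.2% | 5.5% |
| 0.5 | 1.069 | 3.3% | 5.8% |
| 0.7 | 1.092 | 4.3% | 6.1% |
| 0.9 | 1.122 | 5.6% | 6.4% |
| 1.0 | 1.140 | 6.3% | 6.6% |

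**Step 4: check by simulation.** The ordinary t test, with 421 practices per arm and 20,000 runs at ICC 0.05, rejected in 5.4% of runs with near-equal sizes and 6.1% with geometric sizes of mean 1.9 (CV about 0.69, formula value 6.05%). The formula and the simulation agree.

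**Step 5: sensitivity to the ICC (assumed, not in the protocol).** At ICC 0.10 alpha is 6.1% with equal sizes and 8.3% with CV 1.0. At ICC 0.20 it is 7.1% with equal sizes and 10.8% with CV 0.9.

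**The case against.** **The effect is small.** Half a percentage point of alpha at the planning values will seldom change a conclusion. This stands as a statement of size. It does not remove the error: the direction is certain for any positive ICC, which the protocol itself assumes, and the t test gives no protection if the ICC proves larger than planned.

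**Alpha might be thought to reach 7% to 11%.** A reader may infer this from Step 5. Nothing in the protocol supports it. An ICC of 0.20 is four times the planning value, and these figures show only how the error would grow.

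**Every analysis might be thought to ignore clustering, including the ANCOVA and the cost bootstrap.** The protocol does not say so. The ANCOVA is described only as adjusted for arm, without an error structure. The bootstrap is called non-parametric, without a resampling unit; average costs per doctor are a summary, not a resampling rule. These are silences that a SAP could fill. The established error is confined to the named t tests.

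**The analysis method could be left to the SAP.** The choice among adjusted methods could. But the protocol is not silent here: it names a test, and that test does not fit its design.

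**The fix might be thought to be wording only, since the practice identifier drives randomisation.** The insurer must hold that identifier, but the variables listed under Initial collection include no practice code. The insurer adds the allocated arm to the list of doctors, variables were chosen to avoid direct identification, and a university department analyses the data. A practice code in the analysis file is therefore not documented.

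**Conclusion.** The concern holds for the primary 12-month volume, the 3-month volume, the broad-spectrum volume and the two age subgroups. The named test contradicts both the randomisation by practice and the protocol's own sample-size reasoning, and the 5% alpha claimed for the hierarchy is not kept.

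The size is modest. Alpha is about 5.5%, with intervals about 2% too narrow, on the protocol's ICC and mean practice size, assuming equal sizes and two-sided testing. It is about 6.1% to 6.4% at the same ICC if the CV of practice size is 0.7 to 0.9, which is an assumption. Over that range of sizes, alpha would be higher only if the ICC exceeds the planned 0.05. The case for correction rests on the contradiction in the confirmatory analysis, not on a large numerical distortion.

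**What to change.** 1. Replace the t tests for the primary and the compared secondary volumes with a doctor-level linear model containing arm and accounting for practice, by a random practice intercept or by practice-level cluster-robust standard errors. Either keeps the target quantity, the difference in mean DDD per doctor. The choice between them can be made in the SAP, provided the protocol states that clustering by practice is accounted for.
2. Use the same approach in the ANCOVA of doctor factors. Some of these, such as commune type and solo or group practice, vary mainly between practices.
3. State that the cost-effectiveness bootstrap resamples practices, since no resampling unit is given.
4. Add a pseudonymised practice code to the variables that the insurer extracts, before extraction. Without it the analysts could not make the correction later.

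Reporting the observed ICC would also be useful as a check on the planning value, but is not needed to remove the error.

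The cost is one extra variable in the extract, to be fitted to the existing rules against identification, and slightly wider intervals: about 2% at the protocol's inputs and about 4% to 6% under the assumed unequal sizes. No additional doctors or visits are required by this change.
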